However, since the BAS project was planned and carried through, several reports have been published describing that interventions maintaining or enhancing patients’ physical activity level were successful in decreasing stress and increasing quality of life as well as psychological well-being [18]. Anti-depressant effects have also been reported to be caused by exercise in self-referred cancer patients undergoing chemotherapy [19]. Level of physical activity as well as sleep hours relate to psychological well-being and quality of life in cancer patients [20]. Therefore, we wanted to study whether the stress management offered in the BAS project could be improved using a supplement whereby the counsellors performing the intervention specifically worked with motivating the participants to maintain or increase their physical activity level during and after adjuvant/curative treatment. Further, since there is a lack of knowledge regarding individual stress-management interventions in diagnoses other than breast cancer we decided to include various cancer diagnoses, as well as both men and women. In addition, since studies reporting on the cost-effectiveness of stress-management interventions by means of cost-utility analysis (CUA) are scarce, the interventions in the stepped-care approach will be evaluated using CUA.

This paper presents the design of a randomized controlled trial evaluating the psychosocial effects and cost-effectiveness of an individual stress-management intervention, using a stepped-care approach, for patients with various cancer diagnoses. The intervention is based on CBT, and includes encouragement to be physically active. The hypothesis is that a low-intensity intervention will be sufficient for half of the individuals to maintain or improve their psychological well-being after treatment. For individuals who continue to have symptoms after low-intensity treatment, it is hypothesized that continued treatment with high-intensity interventions will be more cost-effective than that of the control group, which entails treatment as usual.

Specific research questions are:

• Are there any differences between patients who received an intervention based on CBT and those who did not, as regards intrusive thoughts, avoidance behaviour, anxiety, depression, sleep duration and quality, and/or moderate-vigorous-intensity physical activity level?

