• Is a stress intervention administered at a low or intensive level a cost-effective way to support patients with cancer?

• Is it possible to predict at baseline which patients are in need of a shorter (low level, Step 1) or longer (intensive level, Step 2) intervention?

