### Design

The study is a prospective, longitudinal intervention study with a stepped-care approach whereby patients will be randomized to individual stress-management intervention (I) or control (C), treatment as usual. A stepped-care treatment model seeks to treat patients at the lowest appropriate level in the first instance, only 'stepping up' to intensive/specialist services if clinically required. One of the key concepts in the stepped-care model is that treatment methods of varying intensities are matched to the needs of the individual patient [21]. In Step 1, all patients who are randomized to individual stress management will be given a low-intensity treatment (I-a). Those patients who do not improve after this treatment will be given a more intensive treatment (I-b) in Step 2. This makes the intervention more cost-effective, since the intensity of the treatment is adjusted to meet the needs of the individual patient. For a more detailed overview of the design, see Figure 1.

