#### Step 2 (I-b)

Patients who report clinically significant levels of stress, such as intrusive thoughts/avoidance behaviour (measured using the Impact of Event Scale (IES) [3]) and/or worry and depression (measured using the Hospital Anxiety and Depression Scale (HADS) [24]) at the six-week assessment will be included in Step 2. Step 2 includes more intensive stress management, with the remaining four to seven sessions devoted to the themes “What is stress?”, “What are the symptoms of stress?” and “Irritability, relationships, the body and pleasure, as well as an orientation towards the future”. These topics are based on an earlier intervention [25]. At all sessions the counsellor will motivate the patient to maintain or increase his or her physical activity level during and after the cancer treatment. At the final session, the counsellor will evaluate the patient’s use of the material and ability to manage his or her stress reactions.

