### End-points and statistical analysis

Power calculations have been done for the IES based on data from another study [23]. On the basis of these conditions (power = 0.8, p = 0.05 and effect size = 0.59), at least 128 patients must be included in each group to detect a significant difference on the IES. To account for the expected dropout and loss of follow-up rates of 15%, we intend to include 300 patients. ANOVA will be used to analyse differences between groups and for repeated measures over time of the continuous variables, while nominal (categorical) variables will be tested using chi square (exact). Although all the criteria for normal distribution are not met with this selection, the parametric tests are sufficiently robust to be used. Patients’ levels of stress-related symptoms will be categorized according to standardized cut-off points. A hierarchical linear regression analysis will be used to examine which variables predict stress symptoms and the utilization of health care services, as well as sick leave and return to work. Net values of the total health care costs will be calculated for the intervention and control groups. Cost–utility analysis (CUA) using quality adjusted life years (QALYs) is a general approach in health economic evaluation [34,35]. QALY is an overall measure of health outcome that weighs a patient’s life expectancy against an estimate of his or her HRQoL score (measured on a 0–1 scale). Cost-effectiveness ratios (CERs) will be calculated as (Δ intervention costs + Δ health care costs)/ Δ QALYs for intervention compared with control. The number of QALYs gained/lost relative to baseline will be calculated for each patient assigned to the intervention or control group as the area under the baseline-adjusted utility curve.

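### Linear regression is specified for return to work, which it does not fit, and no model is named that matches the yes/no Step 2 status in the third research question

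*Protocol article*

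**What the plan says.** The article's section on end-points and statistical analysis assigns one model to four outcomes. It states "A hierarchical linear regression analysis will be used to examine which variables predict stress symptoms and the utilization of health care services", and the sentence continues "as well as sick leave and return to work". It names no logistic, time-to-event or count model. For categorical data it offers an exact chi-square test, and it says that patients' "levels of stress-related symptoms will be categorized according to standardized cut-off points". It also asserts that parametric tests are robust enough although normality is not fully met.

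The third research question, in the Background, asks whether it is possible to "predict at baseline which patients are in need of a shorter (low level, Step 1) or longer (intensive level, Step 2) intervention". The Step 2 section defines that status: patients with clinically significant levels on the IES and/or the HADS "at the six-week assessment will be included in Step 2". According to the Design section only patients randomised to the intervention enter Step 1, so only they can have a Step 1 or Step 2 status. The Abstract gives two years of follow-up.

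**The concern.** A model has to match the form of its outcome, and two of the prediction targets do not match the model named.

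Return to work either has happened or has not, and if it is timed, some patients will not have returned when follow-up ends. Linear regression has no place for an incomplete time. The analyst must drop those patients or give them a value, and the article does not say which. Dropping them removes the slowest returners, who are the patients the analysis most needs. The outcome is also undefined for anyone not working at baseline.

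For the third research question, the status of interest is whether a patient meets a combined criterion on two instruments. Regression on one symptom score shows which baseline variables go with higher scores. It does not give the probability of meeting an and/or criterion, nor show how well baseline data separate the two groups. This is one of three stated research questions, and the Discussion presents support at the right level of care as a main benefit.

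**Working it through.** The plan states no figure for these analyses, so there is none to reproduce. The check compares outcome and model, then sizes the consequences.

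**1. Outcome against model**

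| Target | Form | Model named | Match |
|---|---|---|---|
| Stress symptoms (IES, HADS scores) | continuous | linear regression | yes |
| Service use, sick leave | scale not given | linear regression | defensible for means |
| Return to work | yes/no, or time with follow-up ending at two years | linear regression | no |
| Step 2 status at six weeks | yes/no, intervention arm only | none (exact chi-square is univariable) | no |

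**2. Return to work coded as time**

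The document gives no return times. Assumptions: exponential times, a median of 8 months in the reference group, a hazard ratio of 0.6 for a binary predictor, and complete follow-up to 24 months.

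- Rates per month: λ₁ = ln 2 / 8 = 0.0866; λ₂ = 0.6 × λ₁ = 0.0520.
- Not returned at 24 months, S = exp(−24λ): 12.5% and 28.7%.
- Restricted mean to 24 months, (1 − S)/λ: 10.10 and 13.71 months; difference 3.6.
- Mean among returners only, 1/λ − 24·S/(1 − S): 8.11 and 9.57 months; difference about 1.5.

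The same formulas with other assumed medians and the hazard ratio kept at 0.6:

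| Median in reference group (months) | Not returned at 24 months | Restricted-mean difference (months) | Returners-only difference (months) |
|---|---|---|---|
| 4 | 2% vs 8% | 3.1 | 2.1 |
| 8 | 12.5% vs 28.7% | 3.6 | 1.5 |
| 16 | 35% vs 54% | 2.9 | 0.8 |

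The returners-only difference is smaller in every row, and the gap in relative terms grows as more patients remain off work. If non-returners are instead entered at 24 months and follow-up is complete, linear regression estimates the restricted-mean difference itself. The loss therefore comes from dropping non-returners, and that second route fails only when follow-up is incomplete. The plan expects 15% dropout and loss to follow-up.

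**3. Return to work or Step 2 status coded yes/no**

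A simulation used ordinary linear regression on a binary outcome with three standard-normal predictors (assumed log-odds 0.8, 0.6 and 0.4; 300 runs per setting). It gave these shares of fitted probabilities outside 0 to 1:

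- n = 255 (300 × 0.85), event rate 0.5, 0.7, 0.8 and 0.9: about 3%, 6%, 9% and 14%.
- n = 127, event rate 0.3 and 0.5: about 6% and 3%.

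The misfit is real but moderate, and smallest near a rate of one half.

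**4. What the data can support for the third research question**

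- Intervention arm: 300 / 2 = 150 patients (equal allocation assumed).
- After 15% loss: 150 × 0.85 = 127.5, about 127.
- Step 2 share: the Background hypothesises that "a low-intensity intervention will be sufficient for half of the individuals" to maintain or improve well-being. Taking one half as the share stepping up, 127.5 × 0.5 ≈ 64 events, or about 6 predictors at 10 events each.
- With a share of 30% or 70%, the smaller outcome group has 127.5 × 0.3 ≈ 38 patients, or about 3 to 4 predictors.

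The one-half figure is only a guide, because the hypothesis concerns maintained or improved well-being and Step 2 entry concerns a cut-off at six weeks.

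**The case against.** The strongest reply has four parts.

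First, the third research question is not ignored. The planned regression targets stress symptoms, which underlie the Step 2 decision; the scores are to be categorised by cut-offs; and chi-square allows single-variable comparisons. Modelling a continuous score can be an efficient way to find baseline predictors. This stands. A reader might infer that the question would go unanswered, and the document does not support that. What remains is that no named model has Step 2 status as its outcome.

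Second, a reader might infer that linear regression is also wrong for service use and sick leave because such data are skewed with many zeros. The document gives neither scale nor distribution for them. Every patient is scheduled for treatment at the recruiting department, which argues against many zeros in hospital use. Linear regression can validly model means of skewed amounts. A count or two-part model is an option there, and the stated choice is not an error.

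Third, the coding of return to work is not given, and the reference to a quicker return is Discussion language. That is fair, but the mismatch does not depend on the coding: linear regression fits neither the yes/no form nor a censored time. The article's robustness statement concerns normality and answers neither.

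Fourth, an unseen analysis plan may hold the detail. It may well add a model for the third question. For return to work, however, the article makes a positive choice of model, and that choice would still need correcting.

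**Conclusion.** The point holds for two secondary analyses. The linear model stated for return to work does not fit that outcome, and the yes/no Step 2 status has no matching model. The size depends on coding and handling. Under the assumed return times, dropping non-returners reduces differences of 2.9 to 3.6 months to 0.8 to 2.1 months; entering them at 24 months with complete follow-up does not. For a yes/no coding, about 3% to 14% of fitted probabilities are impossible values under the simulation's assumptions. None of these inputs comes from the document, so the figures show direction and order of magnitude only.

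The consequence should not be read more widely. The IES comparison between arms and the cost-utility analysis do not use these models and are unaffected. This is a correction worth making to secondary prediction analyses.

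**What to change.** - **Continuous scores (such as IES and HADS):** keep hierarchical linear regression.
- **Third research question:** logistic regression of meeting the Step 2 criterion at six weeks on baseline variables, in the intervention arm, reporting discrimination and calibration. Fix a short predictor list in advance, about 6 if half step up.
- **Return to work:** state how it is recorded. If timed, use a time-to-event model such as Cox regression among patients working at baseline, with non-returners censored at last follow-up and not dropped. If recorded only as yes/no, use logistic regression in the same patients.
- **Service use and sick leave:** no change is required; stating each scale would help.

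The cost is mainly analysis wording. It should be confirmed that work status at baseline is recorded, and dates of return if the outcome is timed. The drawbacks are a limited number of predictors for Step 2 status and a smaller sample for return to work.

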### Ethical considerations

The study has been approved by the Medical Research Ethics Committee and the Data Inspectorate of Norway (2010/1911). The intervention in the project will be administered by specially trained staff, and will be supervised continuously so that any potentially harmful effects can be detected early in treatment and corrected immediately. Since the design includes a control group who will receive treatment as usual, it will be possible to monitor patients for potentially harmful effects. The questionnaires used in the present study have been chosen with care, in terms of both length and number. Recording physical activity level and sleep using an objective monitor as in the present study has been reported to be feasible and acceptable to cancer patients, and compliance has been reported as high [29].

## Discussion

By screening for intrusion, avoidance, anxiety and/or depression, the intervention at low- or high-intensity level will hopefully help and support the individual patients, both men and women with various cancer diagnoses, at the right level of care. In the present study, using a stepped-care approach, it will be possible to evaluate the effectiveness of both a low-intensity general stress-management intervention and a high-intensity individually tailored stress-management intervention compared to standard care. Further, we will gain knowledge concerning whether the stress-management intervention administered here can motivate the participants to maintain or increase their physical activity level during and after adjuvant/curative treatment. Health care and society stand to gain substantially from the planned intervention programme, in the form of both individualized psychosocial support and increased psychological well-being. This may result in a reduced utilization of health care, preserved work capacity or a quicker return to work. The high-intensity individually tailored support will only be offered to patients who show a clear need, which may be an economically beneficial model, for both the patient and society. For research purposes, it is also important to gain increased knowledge about how to select and deliver effective supportive intervention for patients with various psychological needs and cancer diagnoses. The present study will be integrated within the usual care at the Department of Oncology. This can facilitate the implementation of evidenced-based psychosocial care for cancer patients.

The project has limitations, which should also be noted. Most stress-management interventions have been delivered in group format. The lack of a third group, undergoing the stress-management intervention in a group setting, makes it impossible to compare the effects of different stress-management intervention settings (individual vs. group) on stress symptoms compared to a control group. However, if a third randomization group had been added to the project it would have prolonged the time frame by approximately 12 months, which was not economically justified.
